### Data and statistical analysis

The primary end point will be analyzed according to the intention-to-treat principle using the independent-samples t-test. In addition per-protocol analysis and to adjust for risk factors (such as diabetes, hypertension, smoking, cholesterol level, sex) multivariate regression analysis will be performed. The secondary endpoints are compared using Student’s t-test, Mann–Whitney U test, chi-square test and Fisher’s exact test as appropiate and by multivariate regression models.

All data will be collected independently in a blinded database by an external data management facility (2conduct clinical trials). A p-value of <0.05 will be considered as statistically significant. Data analysis will be performed using SAS 9.3 (SAS Institute Inc.).

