### Primary and secondary outcome

The primary study end point of the HITS-RP study is the incidence of HITS during PCI. Secondary endpoints are changes in CFVR, cardiac biomarkers (cTNI, CK, CK-MB) and hs-CRP in comparison to the initial values, ECG changes, bleeding complications due to the additional thrombocyte inhibiton, and any type of major adverse cardiac or vascular event during one month follow-up. Bleeding complications will be assessed according to the GUSTO criteria (a-severe or life-threatening; b-moderate; c-mild) [18].

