### Power calculation

Based on the results of previous studies [7] we expect 27 HITS on average in the placebo group and 18 HITS in the treatment group. Assuming a standard deviation of 12 in both groups, we will need a sample size of 29 patients to detect the treatment effect with a power of 80% at a two-sided alpha-level of 0.05. To account for drop-outs we have chosen to include 30 patients per group in the study.

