### Patient treatment

All patients receive 100 mg acetylsalicylic acid once daily before PCI and thereafter according to the standards of good clinical practice. Those patients not already taking clopidogrel medication will receive 600 mg immediately after PCI and afterwards 75 mg once daily. A heparin bolus of 70 IU Heparin/kg body weight is given following the insertion of the arterial sheath. All other medication is given at the discretion of the attending cardiologist. After diagnostic angiography with knowledge of the coronary anatomy patients are planned to undergo balloon dilatation with implantation of a stent for a single stenosis. The choice of stent (bare-metal or drug-eluting stent) is left to the discretion of the attending cardiologist. Patients will be randomly assigned to the glycoprotein IIb/IIIa receptor antagonist abciximab or placebo. The study drug will be given as an i.v. bolus of 0.25 mg/kg body weight 10 minutes before PCI followed by a continuous infusion at 0.125 μg/kg/min initiated immediately after the bolus and continued for 12 h. A Doppler guidewire is positioned 1 to 2 cm distal to the stenosis for PCI. At this position the average peak velocity (APV) is recorded. Before and after each interventional step CFVR is measured as the ratio of maximum APV and baseline APV. Maximum hyperemia will be induced by intracoronary injection of 30–40 μg adenosine. The number of HITS will be measured as previously described [7].

After PCI, removal of the sheath is performed according to local practice. Care must be taken to ensure adequate hemostasis.

After 12 and 24 h creatine kinase (CK), creatine kinase-MB (CK-MB), cardiac troponin I (cTNI), hemoglobin (Hb), hs-CRP will be determined and after 24 h also an ECG will be recorded. At 30-day follow-up all cause mortality, myocardial infarction, angina pectoris, new congestive heart failure, and bleeding complications will be assessed. This is the end of the trial.

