### Limitations

Due to the small study size results will be interpreted with caution and in case of reduction of HITS a larger clinical trial will have to follow. Due to statistical reasons, we do not expect a difference in the composite major adverse cardiac event rate (death, reinfarction, target vessel revascularization, new congestive heart failure) between the two study arms.

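### One unrestricted p<0.05 rule covers the primary test, its repeat analyses and every secondary endpoint, so an isolated secondary result could be called statistically significant (minor)

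*Protocol article*

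**What the plan says.** The primary endpoint is HITS during PCI. Under Data and statistical analysis it has one primary test, an intention-to-treat t-test, followed by a per-protocol analysis and a regression adjusted for risk factors. The same section assigns the secondary endpoints a choice of standard two-group tests, "as appropiate and by multivariate regression models". After a sentence on data collection it states: "A p-value of <0.05 will be considered as statistically significant". No endpoint or analysis is exempted.

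Under Primary and secondary outcome: "Secondary endpoints are changes in CFVR, cardiac biomarkers (cTNI, CK, CK-MB) and hs-CRP in comparison to the initial values", followed by ECG changes, bleeding, and major adverse cardiac or vascular events to one month. That is eight named endpoints: CFVR, cTNI, CK, CK-MB, hs-CRP, ECG, bleeding and MACE. Patient treatment gives the blood sampling times: "After 12 and 24 h creatine kinase (CK), creatine kinase-MB (CK-MB), cardiac troponin I (cTNI" and so on, with hs-CRP in the same list.

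Power calculation concerns HITS only, "with a power of 80% at a two-sided alpha-level of 0.05". Limitations adds: "Due to the small study size results will be interpreted with caution".

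**The concern.** The point concerns a rule that the article states, not an adjustment that it omits. Followed literally, the rule lets any secondary comparison with p<0.05 be declared statistically significant whatever the HITS result, and lets the per-protocol or adjusted HITS analysis be declared so on the same footing as the primary test.

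The trial has 30 patients per group and is powered only for HITS. If HITS showed no difference, a chance finding on one marker at one sampling time could be reported as a significant effect of abciximab within the plan's own terms. The caution in Limitations rests on study size. It neither ties secondary results to the primary one nor calls them exploratory.

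**Working it through.** **1. The plan's own figure.** The inputs, from Power calculation, are: "we expect 27 HITS on average in the placebo group and 18 HITS in the treatment group" (difference 9); "Assuming a standard deviation of 12 in both groups, we will need a sample size of 29 patients"; 80% power; two-sided alpha 0.05.

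- Normal approximation: n = 2 × (1.960 + 0.842)² × 12² / 9² = 27.9, so 28 per group.
- Noncentral t: 29 per group gives 80.1% power, and 30 per group gives 81.5%.

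The stated 29 therefore reproduces as a per-group number. The 0.05 in the design belongs to this single test.

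**2. Number of secondary comparisons.** Four markers (cTNI, CK, CK-MB, hs-CRP) × two times = 8. Adding CFVR, ECG, bleeding and MACE, one each, gives 12. With one comparison per marker the count is 8. Testing each marker at both times is an assumption; the article does not say so. The regression repeats are not counted. They would add to the figures, but by an amount not worked out here.

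**3. Chance of at least one two-sided p<0.05 when all secondary nulls are true.** For m independent tests this is 1 − 0.95^m:

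- m = 8: 1 − 0.95^8 = 33.7%
- m = 12: 1 − 0.95^12 = 46.0%

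The endpoints are correlated, but the article gives no correlation. Simulation with equicorrelated normal test statistics (200,000 sets per setting; the zero-correlation row is the exact formula) gives:

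| Assumed correlation | 12 tests | 8 tests |
|---|---|---|
| 0 | 46.0% | 33.7% |
| 0.3 | 39.7% | 29.9% |
| 0.5 | 31.8% | 25.0% |
| 0.7 | 23.4% | 19.0% |
| 0.8 | 18.6% | 15.7% |
| 0.9 | 13.6% | 11.9% |

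With an assumed block structure (six CK, CK-MB and cTNI tests correlated at 0.8, two hs-CRP tests at 0.7, the other four independent), the figure for 12 tests is 35.6%.

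**4. Two corrections that lower the figure.**

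- *Rare events.* Fisher's exact test at 30 versus 30 has a true size of 0.1% at a 5% event rate, 0.9% at 10% and 2.2% at 20%. Taking three of the 12 tests at about 1% and the rest at 5%, all independent: 1 − 0.95^9 × 0.99^3 = 38.8%.
- *Direction.* A false benefit needs the favourable tail only, 2.5% per test. Leaving out bleeding and MACE, the ten efficacy tests give 1 − 0.975^10 = 22.4% if independent, and less if positively correlated.

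**The case against.** The strongest reply is that multiplicity control for secondary endpoints is commonly left to a full protocol or SAP, neither of which is shown, and that the threshold sentence is a conventional one. The first part stands: a missing adjustment or hierarchy is no fault in an article of this kind. What remains is the breadth of the sentence that is there. A later SAP could narrow it, but would then depart from the published rule.

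Four stronger readings are tempting and are not supported.

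- A reader might infer that the trial's type I error is inflated. It is not. There is one primary endpoint, one named primary test and one power calculation at 0.05.
- A reader might take the 23% at correlation 0.7 as a lower bound. It is not. At 0.8 to 0.9 the figure falls to about 19% to 14%, and high correlation among three injury markers in the same patients is plausible.
- A reader might infer that the section on clinical implications already plans to claim less myocardial damage and inflammation from secondary results. That text is conditional and describes what would follow if the hypothesis held. Limitations ties a larger trial to a reduction in HITS, not to any secondary p-value, and expects no MACE difference.
- A reader might treat the whole 14% to 46% as the risk of a false claim of benefit. It counts both directions and includes the safety endpoints. It also needs every null to be true, and the Discussion itself reports more bleeding with abciximab in earlier trials. Dropping bleeding leaves 11 tests, 43% if independent.

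**Conclusion.** The point holds as a minor one about wording. The stated rule reaches beyond the primary test, and nothing else in the article restricts it. For 12 two-sided secondary tests with all nulls true, the chance of at least one nominally significant result is roughly 14% to 46% under common correlations of 0.9 to 0. Even the low end is nearly three times the nominal 5% (13.6 / 5 = 2.7). Counting rare-event tests at their true size lowers the range, and the chance of a false benefit on the ten efficacy tests is about 22% or less.

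The count of 12 and the correlations are assumptions. The sample size, the primary analysis and the primary conclusion are unaffected.

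**What to change.** Replace the threshold sentence in Data and statistical analysis with wording such as:

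> *The two-sided 0.05 significance level applies only to the primary intention-to-treat t-test of HITS. Per-protocol and covariate-adjusted analyses of HITS are sensitivity analyses. Secondary endpoints are exploratory and are reported as between-group estimates with 95% confidence intervals; any p-values are nominal. Bleeding and MACE are reported descriptively with confidence intervals.*

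Secondary p-values need not be banned; whether to print them is a matter of reporting style. If the sponsor wants one confirmatory secondary claim, it should be named in advance and tested only if the primary test is significant.

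The change needs no patients or data and should be made before unblinding. The downside is that an isolated secondary p<0.05 can no longer be called a statistically significant effect.

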## Discussion

Coronary microembolization is a frequent event in ischemic heart disease, occurring artificially during coronary interventions. Especially patients with multivessel coronary artery disease, more than 20 microemboli, and high inflation pressure during PCI are at risk for pNSTEMI [7]. Thus, the protocol of the HITS-RP study is focused on patients undergoing elective PCI for stable CAD.

It is important to note that data for the use of filter devices during PCI were disappointing and no significant protection against microembolization was achieved in previous studies [19]. In consequence novel treatment strategies of preventing patients from pNSTEMI are desired.

Numerous studies demonstrated the effect of anti-platelet agents in patients with stable angina pectoris or acute coronary syndrome for attenuation of myocardial damage and reduction of adverse events [20,21]. However, it is still unclear whether the respective agent is able to reduce the formation of coronary microemboli. The glycoprotein IIb/IIIa receptor antagonist tirofiban reversibly suppressed HITS in the cerebrovascular circulation [22]. Thus, this clinical study is designed to identify a target for drug therapy of coronary microembolization and its consequences. In previous clinical trials, the benefits of abciximab infusion were achieved at the risk of increased bleeding [16]. It is necessary to mention that also the safety of abciximab infusion when added to antiplatelet therapy with aspirin and clopidogrel is an important question of the HITS-RP study.

### Limitations

Due to the small study size results will be interpreted with caution and in case of reduction of HITS a larger clinical trial will have to follow. Due to statistical reasons, we do not expect a difference in the composite major adverse cardiac event rate (death, reinfarction, target vessel revascularization, new congestive heart failure) between the two study arms.

### Clinical implications of the hypothesis

Clinical findings suggest that coronary microembolization and pNSTEMI are frequent periprocedural complications. Relevant numbers of microemboli during cardiac interventions could also be detected in the cerebrovascular circulation [23].

Administration of abciximab could protect the myocardium and maybe also the cerebrovascular system. It may reduce the incidence of myocardial damage and also the inflammatory reaction associated with myocyte necrosis. Because of its ease administration and general availability this treatment approach could have a high potential in clinical practice.

## Abbreviations

APV: Average peak velocity; CAD: Coronary artery disease; CFVR: Coronary flow velocity reserve; CK: Creatinine kinase; CK-MB: Creatinine kinase muscle/brain; cTNI: Cardiac troponin I; ECG: Electrocardiogram; GP IIb/IIIa: Glycoprotein IIb/IIIa; Hb: Hemoglobin; HITS: High intensity transient signal; hs-CRP: High-sensitivity C-reactive protein; PCI: Percutaneous coronary intervention; pNSTEMI: Procedural associated non-ST elevation myocardial infarction.
